## Abstract

**Background:**

Contemporary management of uncomplicated type B aortic dissections (uTBAD) is based on the acuity and various morphological features. Medical therapy is mandatory, while the risks of early thoracic endovascular aortic repair (TEVAR) are balanced against the potential for rupture, complex surgery, and death. Improved aortic morphology following TEVAR is documented, but evidence for improved overall survival is lacking. The costs and impact on quality of life are also needed.

**Methods:**

The trial is a randomized, open-label, superiority clinical trial with parallel assignment of subjects at 23 clinical sites in Denmark, Norway, Sweden, Finland, and Iceland. Eligibility includes patients aged ≥ 18 with uTBAD of < 4 weeks duration. Recruited subjects will be randomized to either standard medical therapy (SMT) or SMT + TEVAR, where TEVAR must be performed between 2–12 weeks from the onset of symptoms.

**Discussion:**

This trial will evaluate the primary question of whether early TEVAR improves survival at 5 years among uTBAD patients. Moreover, the costs and the impact on quality of life should provide sorely needed data on other factors that play a role in treatment strategy decisions. The common Nordic healthcare model, with inclusion of all aortic centers, provides a favorable setting for carrying out this trial, while the robust healthcare registries ensure data validity.

**Trial registration:**

ClinicalTrials.gov NCT05215587. Registered on January 31, 2022.

## Administrative information

Note: the numbers in curly brackets in this protocol refer to SPIRIT checklist item numbers. The order of the items has been modified to group similar items (see http://www.equator-network.org/reporting-guidelines/spirit-2013-statement-defining-standard-protocol-items-for-clinical-trials/).

## Introduction

### Background and rationale {6a}

Theincidence of a Stanford type-B thoracic aortic dissection (TBAD) is estimated at 3.9–6.0 per 100,000 person-years, although this may be an underestimate [1–3]. These account for approximately 30–40% of all types of aortic dissection [4]. The diagnosis of TBAD is further classified with respect to timing: acute, ≤ 14 days, subacute, 15–90 days, and chronic, > 90 days. Approximately 40–50% of TBADs are considered complicated and defined by the presence of one or more of the following: rupture and/or hypotension/shock, organ malperfusion, rapid aortic expansion, paraplegia/paraparesis, peri-aortic hematoma, or intractable pain or hypertension [2, 5]. The definition of intractable is somewhat vague in the literature, yet the guidelines from the American Society for Vascular Surgery suggest a duration of > 12 h despite medical therapy [6]. In the absence of these complications, the dissection is considered uncomplicated. In-hospital survival for these patients has been reported as approximately 90% [7].

Open surgery has previously played a role in the treatment of TBAD patients, but its dismal outcomes, particularly when compared to medical treatment, have led to changes in strategy [8–10]. Contemporary TBAD management is dependent upon the above-mentioned factors, i.e., complicated or uncomplicated, acute or chronic, as well as accompanying comorbidities. An underlying and universal component for all these patients is standard medical therapy, which includes antihypertensive therapy, typically β-blockers, in order to mitigate aortic wall stress and false lumen pressures, as well as pain relief [11]. Furthermore, lifestyle improvements and cardiovascular risk profile modification are recommended.

The introduction of thoracic endovascular aortic repair (TEVAR) in 1994 radically changed the treatment of TBAD, and TEVAR is now the recommended therapy for complicated TBADs, thoracic aortic aneurysms, and traumatic thoracic transections, among others [12, 13]. To date, the use of TEVAR in the treatment of uncomplicated TBAD is uncertain, if not controversial. Several analyses have found that TEVAR confers improved aortic remodeling and possibly survival, albeit with the implied and inherent procedural risks of intervention, including paraplegia, retrograde dissection, and death [14, 15].

There are two relevant randomized clinical trials (RCTs), addressing the issue of early TEVAR among TBAD patients. The Acute Dissection: Stent graft OR Best medical therapy (ADSORB) trial, notably underpowered, randomized a total of 61 patients from 17 European centers with acute uTBAD [16]. There were no aortic ruptures at 1 year in either arm of the trial, while TEVAR was associated with improved thrombosis of the false lumen and reduction of its lumen. The Investigaton of Stent Grafts in Aortic Dissection (INSTEAD) trial included 140 patients in the subacute phase [17]. The overall survival at two years was statistically equivalent, 95.6% in the OMT (optimal medical therapy) group and 88.9% in the TEVAR plus OMT group. The long-term results from the extended INSTEAD-XL found a non-significant absolute reduction in all-cause mortality of 8.2% at 5 years for those patients who underwent TEVAR [18]. The authors performed an additional Landmark analysis, thus focusing only on outcomes from years two to five, and identified an absolute mortality reduction of 16.9%.

The conclusions from the retrospective and above-mentioned RCTs have not been persuasive enough for the European Society of Vascular Surgery to render a higher recommendation than “TEVAR may be selectively considered” for those patients presenting with uncomplicated type B aortic dissections [2]. This is furthermore echoed by a recent international survey regarding the preferred treatment of uTBAD, in which 54.8% of respondents answered that they do not routinely use TEVAR, as opposed to 37.4% who prefer this strategy. More importantly, 88.6% of respondents agreed that equipoise was present and that an RCT was needed [19].

Notwithstanding the clinical implications of various treatment algorithms, there are two further relevant aspects regarding the treatment of uTBAD patients that must be considered. First, the economic ramifications of potential interventions, readmissions, reinterventions, and rehabilitation are complex. A recent Canadian study demonstrated that the median and total yearly costs of treating aortic dissection have increased beyond the rate of inflation, while rehabilitation constitutes a significant portion of these costs [20]. Second, and somewhat coupled to the first, is the quality of life of these patients. Although evidence is limited, patients surviving a dissection have reported poorer levels of mental health and sexual function [21]. These two issues must be accounted for in any future societal appraisals of the evidence and evaluations of the costs and benefits.

### Objectives {7}

The primary objective is to compare the overall survival at 5 years between subjects treated with standard medical therapy (SMT) or SMT + subacute TEVAR. The secondary objectives include the comparison of aortic-related mortality, neurological injury, aortic intervention, readmissions, reinterventions, quality-of-life (QoL), costs, and 10-year survival.

### Trial design {8}

The trial is a randomized, open-label, superiority clinical trial with parallel assignment of subjects in multiple sites in Denmark, Sweden, Norway, Iceland, and Finland. Recruited subjects will be randomized to either SMT exclusively or TEVAR + SMT.

## Methods: participants, interventions, and outcomes

### Study setting {9}

The study encompasses all of the 23 academic and tertiary aortic centers in the five above-given Nordic countries. These sites represent the major referral centers for medical and surgical treatment of aortic pathology. An updated list on participating sites, recruitment, and contact information is found on the trial [22].

### Eligibility criteria {10}

#### Inclusion criteria

All subjects, aged 18 or greater at the time of informed consent signature, admitted or referred to the participating cardiovascular Sites with an uTBAD of less than four weeks duration.

#### Exclusion criteria

Subjects with no signed informed consent.Subjects presenting with a *complicated* type B aortic dissection according to the above definition.Subjects previously treated in their descending aorta, either open surgery or TEVAR.Subjects with pre-existing thoracoabdominal aortic aneurysm.Subjects with traumatic aortic dissections.Subjects with an established connective tissue disease at the time of randomization, including but not limited to Marfans and Loeys-Dietz syndrome.Subjects with a clinically estimated life expectancy < 2 years.Subjects with dementia.Pregnant or nursing subjects.Subjects with current sepsis.Subjects currently participating in other clinical interventional trials.

### Who will take informed consent? {26a}

The process of informed consent will be carried out by an approved primary investigator from any of the participating sites. Consent procedures follow local and national regulatory guidelines. A copy of the informed consent document will be given to the subject for their records.

### Additional consent provisions for collection and use of participant data and biological specimens {26b}

No additional or ancillary data will be obtained and, thus, no further consent will be obtained.

## Interventions

### Explanation for the choice of comparators {6b}

Despite evidence from retrospective and descriptive studies suggesting long-term benefits for early TEVAR intervention among uTBAD subjects, the underlying unanswered question is whether TEVAR confers a benefit of survival. The two previous RCTs, mentioned above, were underpowered to address this issue. Despite the potential theoretical and procedural advantages of various composite endpoints, it was determined that a trial based on a clearly expressed question with a binary outcome will have the most clinical impact. Similarly, focus on the albeit interesting, but not essential, endpoint of aortic morphological changes and imaging findings, would complicate the pragmatic design of this trial.

### Intervention description {11a}

#### Standard medical therapy (SMT)

Contemporary standard medical therapy for TBAD consists of antihypertensive agents and pain relief. The choice of the specific agents will be left to the discretion of the individual treatment sites/surgical team, based on the individual subject’s prior and current therapy and tolerance to various medical regimens. While the goal is to reduce the systolic blood pressure to between 100 and 120 mm Hg and the pulse rate below 60 beats/minute in the acute phase, the advocated first-line therapy consists of intravenous β-blockade, with calcium channel antagonists and/or renin-angiotensin inhibitors as alternatives. Pain relief is furthermore critical in order to mitigate activation of the sympathetic nervous system and resultant tachycardia and blood pressure elevation. Anxiolytic medication may also be used in this role.

Long-term SMT is essential and, although not evaluated in any clinical trials, the target blood pressure is 120/80 mmHg [23]. All subjects will be equipped with a home blood pressure apparatus in order to measure and record their values. As detailed below, these measurements will be recorded in the electronic database for all subjects at follow-up consultations.

Clearly, medical therapy for aortic dissection is a complex and unresolved research topic in and of itself, and individual-specific therapy can only be supported by guidelines from the European Society of Vascular Surgery and the European Society of Cardiology. Consideration in the trial was given to the connotations of “best” or “optimal” medical therapy, as well as kindred RCT protocols, e.g., Asymptomatic Carotid Surgery Trial-1 (ACST-1) [24], and the ramifications of these definitions vis-à-vis endpoint determination. Because of the recognized local differences in medical therapy and the interest in maintaining the pragmatic nature of this trial, it was determined that the terminology of “standard medical therapy” is most appropriate.

To that end, all sites, investigators, and subjects will be informed of the blood pressure target-oriented nature of this treatment and the following recommendations from the European Society of Vascular Surgery: Initial therapy consists of β-blockers. In subjects who do not respond to β-blockers or who do not tolerate the drug, calcium channel antagonists and/or renin-angiotensin inhibitors can be used as alternatives [2]. In addition to these recommendations for hypertension, efforts should be made to alter and improve lifestyle and cardiovascular risk profiles, including smoking cessation, weight control, and potential treatment of other comorbidities such as diabetes mellitus and ischemic heart disease.

#### Thoracic endovascular aortic repair (TEVAR)

Subjects randomized to TEVAR therapy will undergo placement of an endovascular stent graft in the descending thoracic aorta. The selection of the stent graft is left to the discretion of the treating physicians. While the implicit goal of TEVAR in dissection treatment is to treat the primary tear, certain adjunct proximal and/or distal procedures are often required, e.g., coverage of the left subclavian artery with or without a supplementary left subclavian artery revascularization, e.g., left carotid artery-to-left subclavian artery bypass/transposition or fenestration to left subclavian artery. Any or all adjunct procedures deemed necessary or beneficial by the treating physicians and subjects are allowable under the allocation to the TEVAR subject cohort, as this reflects real-world considerations and the question at hand based on analysis of an intention-to-treat. This includes distal or proximal aortic sealing, as well as Provisional Extension To Induce Complete Attachment (PETTICOAT) or Stent-Assisted Balloon-Induced Intimal Disruption and Relamination in Aortic Dissection Repair (STABILISE) [25, 26].

### Criteria for discontinuing or modifying allocated interventions {11b}

All subjects receive SMT, regardless of the allocated arm of the trial, while the interventional arm will undergo TEVAR treatment within 12 weeks from the onset of symptoms. Some SMT subjects may require surgery, including TEVAR, and the indications for this are up to the discretion of the treating medical and surgical multi-disciplinary team. Indications include, but are not limited to: rupture, rapid aortic expansion, total aortic diameter ≥ 6 cm, pain, refractory hypertension, or malperfused organ(s). Both the procedure and indication will be registered. Note that any intervention predicated on the original aortic pathology is considered as one of the secondary outcomes, i.e., aortic intervention.

### Strategies to improve adherence to interventions {11c}

The premise of this trial is based on both pragmatism and on an intention to treat. Any screened subject with an uTBAD will therefore be considered for recruitment. It is important to underscore, however, that discretion for recruitment is relegated to the sites and investigators, as they must consider the clinical ramifications and the safety of the subject. Significant efforts have been made in informing centers that the limited exclusion criteria should allow for increased enrolment and should discourage arbitrary exclusion based on erroneous protocol interpretations.

### Relevant concomitant care permitted or prohibited during the trial {11d}

As medical therapy is a critical component of both arms of the trial, there are no anticipated egregious therapies that require explicit prohibition. Furthermore, the TEVAR procedure, as defined above, is given broad allowances for adjunct procedures, both planned and ad hoc. All hospital readmissions will also be registered.

### Provisions for post-trial care {30}

All patients enrolled in this trial will be treated and followed in the public healthcare system. There are no private institutions or practitioners involved. Furthermore, all patients will have a documented diagnosis of uTBAD, i.e., there are no otherwise healthy control patients who undergo an experimental treatment. Finally, TEVAR is a recognized and CE (Conformité Européenne) -marked treatment and should in no manner be considered a form of alternative treatment. The right for compensation will thus be considered under the standard avenues and regulations for patient compensation, as covered by each of the national healthcare regulations among the five participating countries.

### Outcomes {12}

The endpoints will be collected from the electronic database and correlated, where relevant, with the individual national board of health registries. These definitions are in accordance with the guidelines from the European Society of Vascular Surgery and the reporting standards document from the American Society for Vascular Surgery [2, 6].

#### Primary outcome

All-cause mortality.

#### Secondary outcomes

##### Aortic-related mortality

Death as a result of aortic rupture or organ malperfusion, or death due to aortic intervention.

##### Aortic intervention

Any open surgical or endovascular intervention performed in any anatomical location, performed for the following indications, which are related to the aortic pathology: aneurysmal degeneration, visceral ischemia, lower extremity ischemia, rupture, or any of the criteria listed above under the definition of a complicated TBAD [2, 27]. Both the timing and indication for the aortic intervention should be recorded. Importantly, the decision for intervention is at the discretion of the treating physician and medical team.

##### Neurological injury

These are divided into two categories: cerebrovascular accidents (CVA) and spinal cord ischemia (SCI). CVAs are defined according to the Society for Vascular Surgery reporting standards and classified as any central neurological complication, ischemic and hemorrhagic. For this project, the modified Rankin scale will be used for classifying stroke severity (Table 1) [28]. Spinal cord ischemia is defined as either ischemic or hemorrhagic resulting in paraparesis or paraplegia. The modified Tarlov scoring scale will be used for the grading of any spinal cord injuries (Table 2) [29]. It is recommended, but not mandatory, that an independent neurologist be consulted for this purpose.

**Table 1 Tab1:** Modified Rankin scale for stroke severity [28]

The scale runs from 0 to 6, running from perfect health without symptoms to death	
0	No symptoms
1	No significant disability. Able to carry out all usual activities, despite some symptoms
2	Slight disability. Able to look after own affairs without assistance, but unable to carry out all previous activities
3	Moderate disability. Requires some help, but able to walk unassisted
4	Moderately severe disability. Unable to attend to own bodily needs without assistance, and unable to walk unassisted
5	Severe disability. Requires constant nursing care and attention, bedridden, incontinent
6	Dead

**Table 2 Tab2:** Modified Tarlov scoring scale for spinal cord injury [29]

Scale	Motor function	Deficit
0	No lower extremity movement	Paraplegia
1	Lower extremity motion without gravity	Paraplegia
2	Lower extremity motion against gravity	Paraplegia
3	Able to stand with assistance	Paraparesis
4	Able to walk with assistance	Paraparesis
5	Normal	Normal

##### Reintervention

Any open or endovascular intervention after the original TEVAR procedure that was related to the dissection. These should be categorized as either planned reintervention, e.g., a staged procedure, or unplanned, which indicates a complication from the original procedure, a failure of the device, or progression of disease.

##### Quality of life

The quality of life will be assessed with the three following self-assessment forms:The EuroQOL-5D-5L instrument from the EuroQol Group, comprised of five dimensions with five levels of scoring that can be combined into a five-digit number of description [30].The Hospital and Anxiety Depression Score (HADS) [31].The 12-Item Short-Form (12-SF) Health Survey [32].

#### Economic evaluation

The economic evaluation will be performed from a payer/healthcare point of view, including resource use associated with healthcare, intervention, and medication, whereas broader potential consequences for society, i.e., effects on productivity, will not be included. During the course of the trial, the accumulated costs will be measured per treatment arm from the participating hospital´s administrative/controlling/billing systems. As far as possible, the following resource use items will be included and captured as accumulated costs from the hospital’s cost-per-subject system on all outpatient and inpatient visits:Costs for healthcare staffSubject-specific costs for primary and secondary endovascular and surgical procedures postoperative care unit costsCosts of drugs during surgery and postoperative careCosts of anesthetic procedures and blood transfusionsAdditional diagnostic procedures from the radiology and clinical physiology departments and from clinical chemistry.

The costs for healthcare staff will comprise the full wage costs, including costs for social security. Costs for each endovascular and surgical procedure will be retrieved individually, and, as far as possible, be based on the price per minute according to the hospital’s cost-per-subject systems.

Changes in health status will be assessed in terms of quality-adjusted life-years (QALYs), which combine the time spent in a specific health state with the corresponding.self-assessed health-related quality of life (HRQoL), as derived from the EuroQOL EQ-5D-5L questionnaire. Time is measured in years and the HRQoL is measured on an index scale ranging from 0 (equivalent to being dead) to 1 (best possible health state). The total number of QALYs will be calculated by multiplying the HRQoL index score (QALY weight) by the time spent in each health state. Group differences in total costs will be calculated and divided by the difference in QALYs in the interval from baseline until the end of the study, and the incremental cost-effectiveness ratio will be calculated as follows:$$(\mathrm{CostTEVAR }-\mathrm{ CostSMT})/(\mathrm{QALYsTEVAR }-\mathrm{ QALYsSMT}) =\mathrm{ \Delta Cost}/\mathrm{\Delta QALY}$$

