### Sample size {14}

The literature supports an overall estimated 5-year survival for TBAD subjects of approximately 80%, i.e., a 5-year mortality of 20% [33]. The above-mentioned INSTEAD-XL clinical trial identified a reduction in 5-year mortality from 19.3 to 11.1% for those who were randomized to TEVAR, corresponding to a hazard ratio of 0.52 [18]. The estimate was not statistically significant, possibly due to a low sample size.

The primary analysis will be based on the intention to treat principle using the full analysis set and all-cause mortality events as confirmed by the local investigator. The primary objective of the study is to determine the superiority of TEVAR versus SMT in reducing the incidence of all-cause mortality. Assuming a true hazard ratio of 0.52 between TEVAR and SMT, using a two-sided alpha of 5%, 80 subjects with primary endpoint events will provide a statistical power of 80% for the test of all-cause mortality between treatment arms, based on an overall 1:1 allocation between TEVAR and SMT and analyzed with a log-rank test. All Scandinavian countries have registries of vital statistics with a high reliability and almost complete follow-up. Consequently, loss-to-follow-up is expected to be negligible, except for migration, and thus a conservative estimate of loss-to-follow-up is given as 3%.

The study is event-driven. With an estimated annual event rate of 4% for the primary endpoint in the control group and a withdrawal probability of 3%, approximately 550 subjects are estimated to provide the required number of primary events.

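### The QALY difference in the cost-effectiveness ratio is stated without adjustment for baseline EQ-5D-5L: unbiased, but less precise than it need be

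*Protocol article*

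**What the plan says.** The Economic evaluation section commits to a method and prints its formula, the cost difference divided by the QALY difference (TEVAR minus SMT). In words: "Group differences in total costs will be calculated and divided by the difference in QALYs in the interval from baseline" to the end of the study. QALYs come from the EQ-5D-5L index: "The total number of QALYs will be calculated by multiplying the HRQoL index score (QALY weight) by the time" spent in each health state. The word baseline appears only as the start of the interval. Adjustment is neither stated nor excluded.

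On aggregation the section points two ways. Costs are described at arm level: "the accumulated costs will be measured per treatment arm". They are also taken from patient-level records: "captured as accumulated costs from the hospital’s cost-per-subject system on all outpatient and inpatient visits". Neither mean nor per patient is mentioned for either term of the ratio.

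**The concern.** A patient's utility at entry usually predicts utility later. If one arm starts slightly healthier by chance, part of that gap carries through follow-up and enters the QALY difference. That difference is small under the trial's own assumptions and sits in the denominator, so noise in it moves the ratio noticeably. Regression on the baseline index removes the predictable part of the noise.

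The second issue is one of wording. If total costs and QALYs were taken as sums over arms, unequal arm sizes would enter the ratio. With means per patient they would not.

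**Working it through.** **Plan's own figures.** The article states no QALY or utility figure. Its design effect is a hazard ratio of 0.52 with 4% annual control mortality (Sample size). Freedman's formula reproduces the stated 80 events: (1.96 + 0.84)² × (1.52/0.48)² = 7.85 × 10.03 ≈ 79, and 79 × 1.0071 = 79.6, so 80. The yearly rates used below are therefore 0.04 (SMT) and 0.04 × 0.52 = 0.0208 (TEVAR), with 277 patients per arm.

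**Assumptions not in the article.** Mean utility 0.78, the same in both arms and constant over time; utility SD s = 0.15 to 0.25; baseline-to-later correlation ρ = 0.3 to 0.6; utility independent of survival time; exponential survival; a 5-year horizon for every patient.

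**Expected gain.** Let t be survival time capped at 5 years. E[t] = (1 − e^(−5λ))/λ.
- SMT: (1 − e^(−0.2))/0.04 = 4.532 years
- TEVAR: (1 − e^(−0.104))/0.0208 = 4.749 years
- Difference: 0.217 life-years, and 0.217 × 0.78 = 0.169 QALY per patient

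**Unadjusted standard error.** With QALY = u × t, the variance per patient is 0.78² Var(t) + s² E[t²], where E[t²] = 2[(1 − e^(−5λ))/λ² − 5e^(−5λ)/λ].
- SMT: E[t²] = 21.904, Var(t) = 1.367
- TEVAR: E[t²] = 23.332, Var(t) = 0.781
- At s = 0.20: 0.832 + 0.876 = 1.708 (SMT) and 0.475 + 0.933 = 1.409 (TEVAR)
- Standard error of the difference: √[(1.708 + 1.409)/277] = 0.106

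**Part that adjustment removes.** This is ρ² s² × (mean life-years)² × 2/277. At s = 0.20 and ρ = 0.5, with mean life-years 4.640: 0.25 × 0.04 × 21.53 × 0.00722 = 0.00155. The unadjusted variance is 0.106² = 0.01125, so the cut is 14% and the standard error falls from 0.106 to 0.0985, about 7%.

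| s | ρ | Unadjusted SE | Adjusted SE | Variance cut |
|---|---|---|---|---|
| 0.15 | 0.3 | 0.092 | 0.090 | 4% |
| 0.20 | 0.5 | 0.106 | 0.0985 | 14% |
| 0.25 | 0.6 | 0.122 | 0.107 | 23% |

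Simulation over the same ranges gives 3 to 24%, central 13% (standard error 0.107 to 0.100). Simulated raw and adjusted differences have the same mean, so neither is biased.

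**Share of the gain.** The SD of the baseline-driven part is 0.018 to 0.059 QALY, or 10 to 35% of 0.169. Total imprecision is much larger: in the central case the standard error is 63% of the gain before adjustment (0.106/0.169) and 58% after (0.0985/0.169).

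**Longer horizon.** The same formulas at 10 years give a gain of 0.787 life-years (0.614 QALY), a variance cut of 2 to 18% (central 10%) and a baseline-driven SD of 5 to 18% of the gain.

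**Arm sums, if that reading were applied.** With 277 in each arm, sums and means give the same ratio. At 0.78 × 4.749 = 3.704 and 0.78 × 4.532 = 3.535 QALYs per patient, a 279/275 split gives 279 × 3.704 − 275 × 3.535 = 61.3, against 277 × 0.169 = 46.9 when balanced: 31% more. The cost numerator moves as well. If TEVAR raised cost per patient by 30 to 100% (assumed), the ratio itself would change by −19 to −22%; with 275/279 it would change by +37 to +42%. If the cost increase were only 5%, the change would be 1 to 2%.

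**The case against.** The strongest defence is that the section gives the ordinary definition of an incremental ratio, and that covariates, imputation and intervals belong in the full protocol or a health-economic plan, neither of which is shown. It is right that silence on adjustment does not amount to a refusal to adjust, and an unseen plan may already include it. But the section prints a formula and says how its terms will be obtained, so a better version of that stated estimator is a fair recommendation.

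A reader might infer that the unadjusted ratio is distorted by tens of percent. The documents do not support that. Under randomisation, chance imbalance is ordinary sampling error that the standard error already includes. Most of the imprecision remains after adjustment, every utility input is assumed, and the share shrinks as the horizon lengthens. Baseline also falls within four weeks of an acute dissection (Inclusion criteria), so its correlation with utility years later could be at or below the low end of the range.

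A reader might also infer that the protocol specifies arm sums. It does not. Patient-level costing, procedure costs retrieved individually and 1:1 allocation fit a per-patient reading, in which total means a sum over one patient's cost items or health states. No block size is given either, so the likely difference in arm size is unknown. What stands is that the wording allows both readings.

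**Conclusion.** The concern holds as a free improvement to a secondary economic outcome. The stated QALY difference is valid but leaves removable chance variation in the denominator of the ratio. Over 5 years, with the design mortality rates and the assumed utility SD and correlation, adjustment would reduce its variance by about 3 to 24%, central about 13%, with a standard error about 7% smaller. Over a longer horizon the reduction is somewhat less. There is no bias, and the mortality conclusion is not touched. The aggregation wording is an ambiguity to clear up, not a stated error.

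**What to change.** In the health-economic plan or SAP:

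1. Estimate the QALY difference by regressing each randomised patient's QALYs on arm and baseline EQ-5D-5L index (intention to treat), and use the adjusted difference in the ratio.
2. Obtain the interval by resampling patients within arm, keeping each patient's costs and QALYs together and refitting the regression in each resample.
3. State that both differences are in mean cost and mean QALYs per randomised patient.

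The cost is wording only. The baseline index is implied by the QALY definition and costs are already held per patient. Patients without a baseline form need a simple imputation of that covariate. If the correlation proves weak, one degree of freedom is lost and nothing else.
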